### Blinding

This is an open non-blinded study, and the staff performing the study will also take subsequent care of the infants.

### Intervention

Infants will be allocated in one of the two treatment groups in a 1:1 ratio according to the minimization method, using an interactive web-based electronic system.

Infants will be electronically randomized into two groups:Control group (CG): surfactant administration when FiO_2_ > 0.30 on nCPAP (positive pressure 6–8 cmH_2_0) to maintain preductal SpO_2_ between 90 and 95% [1].LUS group (LUSG): surfactant administration when LUS > 8 on nCPAP (positive pressure 6–8 cmH_2_0) to maintain preductal SpO_2_ between 90 and 95% [1].

The LUSG will receive SRT as rescue therapy in case of LUS ≤ 8 but FiO_2_ > 0.30 on nCPAP (positive pressure 6–8 cmH_2_0) to maintain preductal SpO_2_ between 90 and 95%.

The cut-off of LUS > 8 is in agreement with previous studies [3, 4, 11].

### Clinical management

Positive pressure with a neonatal mask and a T-piece system (Neopuff Infant Resuscitator ®, Fisher and Paykel, Auckland, New Zealand) will be used to stabilize the newborns after birth as per routine daily practice. If necessary, infants will start mechanical ventilation in agreement with the European guidelines [1]. In this latter case, subjects will be excluded from the study (see “Exclusion criteria” section).

To better standardize the timing of care after birth, assistance in the delivery room, transfer of the newborn to the NICU, stabilization of the newborn, and the related procedures (positioning of the vascular access, stabilization of ventilatory parameters, thermal homeostasis, etc.) are expected to be completed within the first hour of life.

Once infants with RDS have been screened, enrolled in the study, and assigned to a group (CG or LUSG), LU will be performed as soon as possible between 60 and 180 min of life. In the meantime, patients will be assisted with non-invasive ventilation (nCPAP, positive pressure 6–8 cmH_2_0) and oxygen therapy to maintain preductal SpO_2_ between 90 and 95%. A loading intravenous dose of caffeine citrate (20 mg/kg) will be administered in the first hours of life followed by a maintenance of 5–10 mg/kg/day, as per routine clinical practice.

### Non-invasive ventilation management after the first 180 min of life or after surfactant administration

After the first 180 min of life or once surfactant has been administered, according to the criteria of the randomization group, the newborns can be assisted with nCPAP or other non-invasive ventilation mode (nasal intermittent positive pressure ventilation (NIPPV), bi-level positive airway pressure (BiPAP), high flow nasal cannula (HFNC)) according to the local practice.

### Lung ultrasound procedure

LU will be performed by the attending neonatologist. Centers participating in the study routinely use LU and all the neonatologists are trained for this technique.

LUS will be calculated by performing bilateral longitudinal scans of the chest on the midclavicular, anterior axillary, and posterior axillary line as proposed by Raimondi et al. [12] using high-frequency linear or micro linear (hockey stick) probe (Fig. 2). The focus will be located at the level of the pleural line [13]. A score from 0 to 3 (as proposed by Brat et al. [7]) will be assigned to each scan area based on the ultrasound detected pattern; in case of different score patterns in the same area, the worst will be selected (Fig. 3).

**Fig. 2 Fig2:**
[figure not shown]
Lung ultrasound score chest partitioning

**Fig. 3 Fig3:**
[figure not shown]
Lung ultrasound area score. Lung ultrasound score for each area is attributed according to the following criteria: 0, A-pattern (defined by the presence of only A-lines; panel **A**); 1, B-pattern (defined as the presence of three or more B-lines, well spaced; panel **B**); 2, severe B-pattern (defined as the presence of crowded and coalescent B lines with or without consolidations limited to subpleural space; panel **C**); and 3, extended consolidation (panel **D**)

LU can be performed with the patient in supine position without the need of turning as the posterior axillary line is accessible from the side of the newborn [14].

Surfactant replacement therapy should be given if LUS > 8 in subjects recruited in the LUSG.

### Surfactant treatment

Once criteria for surfactant administration have been met, natural surfactant (Poractant alfa, Curosurf ®, Chiesi, Parma, Italy) will be administered (200 mg/kg) according to the InSURE (Intubation-SURfactant-Extubation), LISA (Less-Invasive-Surfactant-Administration), or IN-REC-SURE (INtubation-RECtruitmen-SURfactant-Extubation) technique in both groups as per the enrollment center protocol.

After surfactant administration, patients of both groups will be extubated within 30 min in the case of the InSURE method and IN-REC-SURE method (in presence of satisfactory respiratory drive) and will continue non-invasive ventilation support as per center protocol.

Infants of both groups may receive a subsequent dose of surfactant (100 mg/kg of poractant alfa) using the same method if they fail non-invasive ventilation again during the following 12 to 24 h as per center standard care.

### Analgesia-sedation

Pharmacological premedication with fentanyl and atropine will be allowed (as per center protocol) and recorded.

### nCPAP ventilation failure criteria

In the NICU, nCPAP will be the standard method of non-invasive support in all infants recruited for this trial. nCPAP failure is defined if any of the following criteria are met: FiO_2_ ≥ 0.30 to maintain a SpO_2_ > 90% for at least 30 min unless rapid clinical deterioration has occurred; respiratory acidosis defined as pCO_2_ > 65 mmHg and pH < 7.20 on an arterial or capillary blood gas sample; and apnea defined as more than four episodes of apnea per hour or more than two episodes of apnea per hour which require bag and mask or Neopuff ventilation [15].

### Mechanical ventilation criteria

Mechanical ventilation (MV) should be started if the patient meets one of the following criteria: pCO_2_ > 65 mmHg and pH < 7.20, or paO_2_ < 50 mm Hg, or FiO_2_ > 0.4 after surfactant administration or in case of apnea (> 4 episodes in 1 h or > 2 episodes in 1 h ventilation with bag and mask or Neopuff), and should continue with the aim of maintaining a pCO_2_ of 55–65 mmHg and a SpO_2_ of 90–95%, in conventional MV, or high frequency ventilation (HFV) [15]. Patients will be extubated as per center protocol.

### Concurrent and supportive therapies

The daily treatment practices of patients enrolled in the study will be performed according to the local guidelines of each center. However, to standardize the most relevant procedures in the participating centers, the fluid intake will be based essentially on changes in body weight, serum electrolyte concentration, and serum osmolality starting indicatively with 70–80 mL/kg and increasing by 10–20 mL/kg/day until reaching approximately 150 mL/kg at the end of the first week of life. Maternal or donor milk will be given from the first day of life; if the infusion of a glucose solution is indicated, the concentration of the latter will be chosen in such a way as to maintain appropriate blood sugar levels; electrolytes will be added only after the first day of life, while the intravenous administration of amino acids and lipids will be undertaken from the first day. In the case of systemic hypotension refractory to fluid therapy, vasoactive drugs will be started depending on the underlying pathophysiology.

Newborns will receive antibiotic prophylaxis once blood cultures have been taken, and it will be suspended after 2 or 3 days once results are negative.

Postnatal steroid treatment may be administered in infants with severe respiratory insufficiency under maximal mechanical ventilation and at high risk of mortality or in infants with evolving or established BPD.

### Primary outcome measure

Primary endpoint will be reduction of the proportion of infants with BPD (Jobe and Bancalari (2001) definition) [10] or death in the LUSG versus CG.

### Secondary outcome measures

Group comparison of proportion of “early” (before 3 h of life as defined by Raschetti [3] et al. and Rodriguez-Fanjul et al.[4]) vs. late surfactant treatment.Need of MV in the first 3 days of life.FiO_2_ before surfactant treatment.SpO_2_/FiO_2_ ratio before surfactant treatment.Proportion of infants needing surfactant treatment.Duration of non-invasive and invasive respiratory support.Proportion of infants who need multiple doses of surfactant.Pharmacological and/or surgical treatment of patent ductus arteriosus (PDA).Pneumothorax (PNX) rate.Length of stay in hospital.BPD rate (using multiple definition) and severity.Mortality rate.

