### Statistical analysis

Clinical characteristics of infants in the CG and LUSG will be described using mean values and standard deviation, median and interquartile range, or rate and percentage. Univariate statistical analysis will be performed using the Student’s *t* test for parametric continuous variables, the Wilcoxon rank-sum test for non-parametric continuous variables, and Fisher’s exact test for categorical variables. A *p* value < 0.05 will be considered statistically significant.

Subsequently, clinical characteristics which are most likely associated with BPD or death will be included in a multiple logistic regression analysis to assess their independent role in predicting clinical outcome. Effect estimates will be expressed as odds ratios (ORs) with maximum likelihood-based 95% confidence limits.

The primary statistical analyses will be performed according to the intention-to-treat principle. The per-protocol analyses will be also performed with an explanatory intent. Major protocol deviations will be reported. Patients without any information available about the primary study endpoint will be classified as failure. Single imputation will be used in case of missing values will be observed for the covariates included in the adjusted and subgroup analyses.

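### If mortality differs between the arms, length of stay and duration of respiratory support are confounded by death under the stated t/Wilcoxon rule; most of these comparisons then tend to favour the arm with more deaths, but for invasive support the direction is uncertain

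*Protocol article*

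**What the plan says.** The section on secondary outcome measures names "Duration of non-invasive and invasive respiratory support" and "Length of stay in hospital", each in one line, and lists "Mortality rate" as a separate item. Death is also half of the primary endpoint, which is BPD "or death in the LUSG versus CG".

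The statistical analysis section gives one approach for continuous variables: Student's t "test for parametric continuous variables" and the "Wilcoxon rank-sum test for non-parametric continuous variables". A p "value < 0.05 will be considered statistically significant".

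The section defining study conclusion ends each infant's participation at discharge, death or withdrawal of consent. The only rule near this topic classifies infants without primary-endpoint information as failures, and it covers the primary endpoint alone. For stay and support duration there is no worst rank, no support-free-days measure, no competing-event analysis and no restriction to survivors.

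**The concern.** Stay and support duration are truncated by death. An infant who dies on day 5 has about 5 days of stay and at most 5 days of support, among the smallest values in the trial. In a t or Wilcoxon comparison where shorter is better, that death is scored as a good result.

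This matters only if the arms differ in mortality, and the article's own rationale allows for that. The Background says that early surfactant improves survival, and the Abstract's discussion says that it lowers mortality. If ultrasound guidance saves infants, those infants add long stays and long support to the study arm, and the benefit can appear as a cost. If it costs lives, the loss can appear as shorter stay. Readers commonly take such outcomes as evidence on resource use and recovery.

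**Working it through.** **The plan's own figure.** The article gives no figure for these outcomes. Its only sample-size figure, 668 infants for 35% v 25% on the primary endpoint, reproduces closely:

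n per arm = [1.96·√(2·0.30·0.70) + 0.8416·√(0.35·0.65 + 0.25·0.75)]² / 0.10² = (1.2702 + 0.5422)² / 0.01 ≈ 329, or 658 in total.

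Power at 334 per arm is 80.7%. The point below does not depend on this; only the 334 per arm is carried forward.

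**Inputs.**
- From the article: 334 per arm, t or Wilcoxon test, two-sided 0.05 (two-sided is taken as usual), observation ending at death.
- Assumed, because the article gives none: survivors' stay lognormal with median 65 days and log-SD 0.3, the same in both arms; time of death exponential with mean 14 days, unrelated to the stay the infant would have had; mortality as in the table.

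**Expected shift in mean stay.** Survivors' mean = 65·exp(0.3²/2) = 68.0 days. Mean observed stay in infants who die is about 13.8 days (14 days, cut slightly because death must come before discharge). The artificial difference is the mortality gap times 68.0 − 13.8 = 54.2 days:
- 8% v 6%: 0.02 × 54.2 = 1.1 days
- 10% v 5%: 0.05 × 54.2 = 2.7 days
- 15% v 8%: 0.07 × 54.2 = 3.8 days

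In each case the arm with more deaths has the shorter mean stay.

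**Share of simulated trials with p < 0.05 for length of stay, no true difference in underlying stay.** Ranges show the spread between repeated runs of 2,000 to 4,000 trials.

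| Mortality | Wilcoxon | t test |
|---|---|---|
| 8% v 8% | about 5% | about 5% |
| 8% v 6% | 7–8% | 8–10% |
| 10% v 5% | 20% | 29% |
| 15% v 8% | 31–34% | 42–46% |

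At 10% v 5% and above, nearly all significant results favour the arm with more deaths.

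**Other assumptions.** With mean stay 70 days (SD 20) and median time to death of 7 or 21 days, a separate simulation counted only results favouring the higher-mortality arm (nominal 2.5%). It gave 14–17% (Wilcoxon) and 22–32% (t test) at 5% v 10% mortality, and 46–59% and 60–77% at 10% v 20%.

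**Invasive support.** The article excludes infants intubated in the delivery room, and all start on nCPAP, so many survivors may have no ventilator days. Suppose 65% of survivors have zero days, the rest are exponential with mean 8 days, and infants who die are ventilated until death (mean 14 days). At 10% v 5% mortality about 15% of trials are then significant by Wilcoxon, and nearly all make the arm with more deaths look worse. The sign is opposite to that for stay, and the cause is again mortality.

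**Check of the remedy.** Ranking death worst in the length-of-stay model, the arm with more deaths is significantly favoured in under 1% of trials in every unequal scenario. The comparison still responds to mortality (about 20% significant at 10% v 5%), but in the right direction.

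**The case against.** The strongest objection is that only a condensed article is available, and the handling of deaths in secondary durations is something an analysis plan often settles. The t/Wilcoxon sentence is a general default that follows a sentence on describing clinical characteristics. It does not name these outcomes, and the intention-to-treat sentence speaks of the primary analyses. A Wilcoxon test in survivors would be compatible with the text.

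Part of this stands. The article does not state that deaths are entered at their truncated durations, and an analysis plan not shown could override the default. But the article is not silent on method: it gives one rule for continuous variables, and that rule is unsuitable for outcomes cut short by death. The survivors-only reading does not rescue it. It showed no bias in simulation because deaths there were unrelated to underlying stay. In practice it conditions on a post-randomisation outcome that the trial's own rationale expects treatment to change.

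Three stronger readings are tempting, and the article does not support them:
- A reader might infer that every duration outcome will favour the arm with more deaths. For invasive support the sign can reverse.
- A reader might infer that a large distortion is to be expected. The article gives no mortality rate; its 35% and 25% refer to BPD or death combined. With a gap of 8% v 6% the inflation is small.
- A reader might infer that the main conclusion is at risk. Death counts as failure in the primary endpoint, and mortality is reported separately and watched at the interim, so an attentive reader has some protection.

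**Conclusion.** The point holds for two groups of secondary outcomes. As the text stands, a mortality difference between arms confounds length of stay and support duration. Stay and total or non-invasive support then tend to look better in the arm with more deaths; for invasive support the direction cannot be predicted.

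The size depends on the mortality gap: none with equal mortality, slight at 8% v 6%, and at 10% v 5% a false signal in about one trial in five (Wilcoxon) or three in ten (t test). These figures rest on assumed stays, death times and death rates. Sample size and the primary analysis are untouched. It is a cheap improvement, not a flaw that threatens the trial.

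**What to change.** State for these outcomes:
1. Respiratory support: days alive and free of invasive support, and separately of any support, up to 36 weeks' postmenstrual age, with deaths ranked worst. The window runs from 77 days (birth at 25+0: 11 weeks) to 43 days (birth at 29+6: 6 weeks and 1 day), so compare within the gestational-age strata already used for randomisation. Say how days after a discharge before 36 weeks are counted.
2. Length of stay: time to discharge alive, with death as a competing event.
3. Raw durations in survivors, descriptively and without a test, beside mortality by arm, so that readers can see whether a difference comes from deaths or from recovery.

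Other rules would also be acceptable, provided that they are fixed in advance and do not score death as a short duration.

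The cost is a little more analysis and slightly less familiar units than plain days. Type and duration of support and mortality are already recorded, and discharge or death marks the end of each infant's participation, so no new assessments are needed. The article reports 213 of 668 infants enrolled on 25 September 2023, so from that position the rule could be set well before the final analysis.

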### Other collected data

For each newborn, the following data will be recorded: gestational age; birth weight; birth weight < 10th percentile; sex; type of delivery; Apgar score at the 5th minute; CRIB score and Silverman score; main pathologies of pregnancy (pre-eclampsia, premature rupture of membranes, clinical chorioamnionitis, placental abruption); mode and parameters of ventilation before SRT; time of surfactant administration; blood gas analysis parameters before SRT; max FiO2 before SRT; minimum SpO2/FiO2 ratio before SRT; type and duration of respiratory assistance (oxygen therapy, nCPAP, BiPAP, HFNC, volumetric ventilation, HFV); antenatal and postnatal steroid treatment; number of surfactant doses; SpO_2_/FiO_2_ ratio at 1, 7 days of life, and at 36 weeks of GA or discharge. In addition, common complications of prematurity will be detected: PDA requiring drug therapy or surgical closure; pneumothorax or other air-leak syndromes; necrotizing enterocolitis (NEC) > 2 grade; BPD; intraventricular hemorrhage (IVH) ≥ 3 grade; periventricular leukomalacia (PVL); retinopathy of prematurity (ROP) of grade > 3; and proven sepsis. Furthermore, mortality and length of stay in NICU will be recorded. BPD diagnosis will be based on the classification of Jobe and Bancalari (2001) [10]. The adapted classification of Papile et al. will be used to classify the severity of IVH [16, 17]; diagnosis of PVL will be made in the presence of cystic areas detected with brain ultrasound at 40 post-conception weeks [18, 19]; ROP will be evaluated in accordance with the International ROP Classification [20]; diagnosis of NEC will be made according to Bell criteria [21]. The diagnosis of sepsis will be based on clinical and laboratory data (total neutrophil count, immature/total neutrophil ratio, concentration of C-reactive protein) confirmed by the presence of at least one positive blood or liquor culture.

Each newborn will be identified with an alphanumeric code (pseudo-anonymization procedure) to guarantee data confidentiality.

In the following, the study period time table is reported (Table 1).

**Table 1 Tab1:** Study period timetable

**Timepoint**	**Study period**						
	**Enrolment**	**Allocation**	**Post-allocation**				**Close-out**
	***Prenatal or postnatal before 180 min of life***	**Postnatal before 180 min of life**	***0–180 min of life***	***24*** ± **2 h of life**	***1 week***** ± 1 day of life**	***36 weeks of GA or earlier if patient is discharged***	***Discharge***
**Enrolment**							
**Eligibility screen**	X						
**Informed consent**	X						
**Allocation**		X					
**Interventions**							
***LUS group*** ***Lung ultrasound and FiO2 evaluation for surfactant need***			X				
***Control group*** ***FiO2 evaluation for surfactant need***			X				
**Assessments**							
***Baseline data*** *** Delivery data***			X				
***Clinical data***			X	X	X	X	
***Lung ultrasound score***			X	X	X	X	
***Blood Gas Analysis (if available, performed ONLY for normal clinical practice)***			X	X	X	X	
***Clinical Outcomes***							X

### Data collection

All study data will be obtained from clinical records and will be electronically entered by the local principal and sub-investigators at each participating site where the data originated, using a validated web-based system. Data integrity will be enforced through appropriate range checks and consistency checks at the time of data entry, before the data are committed to the database. Additional errors will be detected by programs designed to detect missing data or specific errors in the stored data. These errors will be summarized along with detailed descriptions for each specific problem in a data query report, which will be sent to the principal investigator of each site. Data entered into the database will be retrievable for viewing through the data entry application. The audit trail will register all the activities performed by the authorized operators. The type of activity that an individual user may undertake is regulated by the privileges associated with his/her user identification code and password. A complete back up of the primary database will be performed once a week and stored indefinitely on a twin server. Incremental data back-ups will be performed on a daily basis and retained for at least 1 week on-site.

There was no structured plan to promote participant retention.

### Statistical analysis

Clinical characteristics of infants in the CG and LUSG will be described using mean values and standard deviation, median and interquartile range, or rate and percentage. Univariate statistical analysis will be performed using the Student’s *t* test for parametric continuous variables, the Wilcoxon rank-sum test for non-parametric continuous variables, and Fisher’s exact test for categorical variables. A *p* value < 0.05 will be considered statistically significant.

Subsequently, clinical characteristics which are most likely associated with BPD or death will be included in a multiple logistic regression analysis to assess their independent role in predicting clinical outcome. Effect estimates will be expressed as odds ratios (ORs) with maximum likelihood-based 95% confidence limits.

The primary statistical analyses will be performed according to the intention-to-treat principle. The per-protocol analyses will be also performed with an explanatory intent. Major protocol deviations will be reported. Patients without any information available about the primary study endpoint will be classified as failure. Single imputation will be used in case of missing values will be observed for the covariates included in the adjusted and subgroup analyses.

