### Sample size

The percentage from international databases of infants with GA between 25^+0^ and 29^+6^ weeks expected to die or to develop BPD derived is approximately 40% using the Jobe and Bancalari (2001) definition [9, 10].

In a retrospective analysis of our data, the percentage of composite outcome of BPD and death at participating centers was 35%.

Assuming the percentage of newborns with death or BPD is 35% (the most conservative condition) in the control group and a decrease to 25% in the experimental group, a sample size of 668 children (334 per arm) is required to obtain a statistical power of 80% with alpha 0.05.

An interim analysis will be planned after 167 infants per arm are enrolled (334 total infants enrolled). Based on the results of the interim analysis, the study will continue to be carried out as follows:1: If the statistical *Z* test gives a value equal to or less than 0.01, the study will be terminated for futility;2: If the statistical *Z* test gives a value equal to or greater than 2.75, the study will be terminated for efficacy;3: If the statistical *Z* test gives a value less than 0.41 or higher than 0.8, the study will be continued until the previously calculated sample size is equal to 668.4: If the statistical *Z* test gives a value equal to or higher than 0.41 and equal to or less than 0.8, the final sample size will be modified, but without exceeding the maximum threshold of 1.5 times the expected initial size (sample size max: 1002).

Sample size calculations and trial simulations have been performed with R.

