### Randomization

Newborns will be allocated to one of the treatment groups (LUSG or CG) in a 1:1 ratio via a central electronically generated procedure by the e-clintrials platform (https://www.eclintrials.org/ect/) managed by [name]. The researchers will login to the platform using their personal username and password. Then a randomization form will be completed in order to verify the presence of the inclusion criteria and the absence of the exclusion criteria. Once the patient’s eligibility is confirmed, the portal will carry out an automatic randomization. Randomization is stratified by center and gestational age.

A block randomization method will be used to guarantee an adequate sample number even for the lowest GAs (25^+0^ to 26^+6^ weeks or 27^+0^ to 29^+6^ weeks).

A monthly accrual report about the study will be sent to the participating centers.

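### BPD severity is an ordered outcome, but the only test named for categorical variables ignores order; a stated ordinal analysis would give direction, an effect size and, under a common shift, more power

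*Protocol article*

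**What the plan says.** The protocol article's Secondary outcome measures include "BPD rate (using multiple definition) and severity". The Statistical analysis section assigns univariate tests by type of variable. Continuous variables get the t test or "the Wilcoxon rank-sum test for non-parametric continuous variables". All others fall under Fisher's "exact test for categorical variables". No separate rule covers ordered categories. The only model described is a multiple logistic regression for BPD or death, which does not address severity.

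The primary outcome is the binary composite of BPD or death. The Sample size section is built on that composite alone and states that "a sample size of 668 children (334 per arm) is required to obtain a statistical power of 80% with alpha 0.05". No number of grades, grade distribution, expected effect or power is given for severity.

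**The concern.** Grades of severity have a natural order. Fisher's test on a table of several grades by two arms returns the same p value however the grades are relabelled, so a consistent move towards milder disease earns no more credit than an equally large scatter across grades. The result carries no direction and no estimate. The trial's hypothesis is directional: earlier surfactant should reduce lung injury. Severity is a natural place for a graded benefit to appear, so an order-blind test can miss or under-describe it. The plan already uses a rank test, but not for this outcome.

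**Working it through.** **Inputs from the article (Sample size, Randomization).** 334 infants per arm, 1:1 allocation, alpha 0.05 (taken as two-sided; the article does not say), control rate 35% and "a decrease to 25% in the experimental group", all for BPD or death.

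**Inputs assumed.** Number of grades, control-arm grade split, size and pattern of the severity effect. The article gives none of these.

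**Step 1: the plan's own figure.** With pooled variance, n per arm = [1.96·√(2·0.30·0.70) + 0.842·√(0.35·0.65 + 0.25·0.75)]² / 0.10² = 328.5, so 329 per arm or 658 in total. At 334 per arm the power is 80.7%. The stated 668 reproduces to within 2%. The exact power of the 2 × 2 Fisher test at 334 per arm is 78.4%, so the binary primary comparison is close to its target.

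**Step 2: an effect to carry over to severity.** The planned 35% to 25% corresponds to an odds ratio of (0.25/0.75)/(0.35/0.65) = 0.619 (inverse 1.615). Under a proportional-odds shift, each cumulative odds of being at or below a grade is multiplied by 1.615. Assumed control grades (none/mild/moderate/severe) of 65/17.5/10/7.5% become 75.0/13.4/6.8/4.8%.

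**Step 3: power of the unordered test.** The large-sample stand-in for Fisher's test is the chi-square with grades − 1 degrees of freedom and noncentrality λ = n·Σ(p₁ⱼ − p₂ⱼ)²/(p₁ⱼ + p₂ⱼ). Here λ = 334 × 0.02461 = 8.22. With 3 degrees of freedom and critical value 7.815, power is 66.7% (66.6% by simulation).

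**Step 4: power of the ordered test.** The tie-corrected Wilcoxon rank-sum test, simulated on the same data, has 81.9% power, a gap of 15.3 points. A check with the true multi-grade Fisher test (1,000 runs) gave 67.6% v 80.9%, a gap of 13.3 points.

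**Step 5: vary the assumptions under a common shift** (334 per arm).

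| Assumed control grades | OR | Unordered | Wilcoxon | Gap (points) |
|---|---|---|---|---|
| 70/15/8/7% | 0.62 | 60.8% | 77.8% | 17.0 |
| 65/17/10/8% | 0.62 | 66.9% | 82.2% | 15.3 |
| 70/15/8/7% | 0.70 | 37.4% | 54.4% | 17.0 |
| 65/17/10/8% | 0.70 | 41.0% | 57.1% | 16.1 |

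With BPD assumed at 20 to 35% and 310 to 334 infants per arm, the four-grade gap stays at about 14 to 18 points. Over inverse odds ratios from 1.2 to 1.615, the gap is about 5 to 11 points with three levels, 7 to 18 with four, and 9 to 22 with five (death as the worst level).

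**Step 6: drop the common shift** (control 65/17.5/10/7.5%).

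| Study-arm grades | Pattern | Unordered | Wilcoxon |
|---|---|---|---|
| 75/7.5/10/7.5% | mild cases only reduced | 93.7% | 62.0% |
| 69/17.5/10/3.5% | severe cases only reduced | 47.0% | 27.8% |
| 65/21.5/10/3.5% | severe moved to mild, total BPD unchanged | 54.2% | 7.4% |

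Here the unordered test is ahead by 32, 19 and 47 points.

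**The case against.** The strongest reply is that this is detail for the statistical analysis plan. The article gives one generic sentence sorting tests by variable type, severity is part of one item in a long secondary list, and a plan that is not shown may specify an ordinal method. Severity might also be reported descriptively or cut to a binary, for which Fisher's test is ordinary. This has weight and keeps the point minor. It does not remove it: the article is not silent but states a rule for categorical variables, and that rule suits an ordered grade poorly.

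The second reply concerns size. A reader might infer that the plan throws away about 15 points of power as a matter of fact. The documents do not support that. Every severity input is assumed, a proportional-odds shift is the pattern that favours the ordered test, and Step 6 shows the advantage reversing. The 35% anchor also includes deaths, which have no BPD grade. Lowering the BPD rate and arm size to allow for this leaves the four-grade gap much the same, but the handling of deaths still changes the number of levels and so the gap.

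A reader might also infer that the primary analysis is weakened or that Fisher's test is invalid here. Neither follows: the primary outcome is binary, and Fisher's test controls its error rate.

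**Conclusion.** The point holds in a limited form. As written, the plan compares an ordered secondary outcome with a test that ignores order and yields no direction or estimate. The lack of a directional estimate does not depend on any assumption about effect. The power cost does. It is about 14 to 18 points for four assumed grades, a common shift and odds ratios of 0.62 to 0.70, and about 5 to 22 points over three to five levels and weaker effects. It becomes a gain for the unordered test when the effect is confined to one grade or merely exchanges severe for mild disease. The point is minor, and the sample size and primary analysis stand.

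**What to change.** In the Statistical analysis section, or in the analysis plan if it does not already do so, state that:

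- ordered categorical outcomes (BPD severity) are compared by the tie-corrected Wilcoxon rank-sum test;
- the estimate is a proportional-odds common odds ratio with 95% CI, adjusted for gestational-age stratum and for centre by a method that tolerates small centres, such as a random effect (the article reports 18 active centres, and expects as few as 10 eligible infants in some);
- grade proportions are tabulated by arm, so that a non-uniform effect is visible;
- deaths are either the worst category or excluded, with the choice fixed in advance;
- Fisher's test is kept for unordered and binary variables.

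The cost is a few sentences and no new data. The article reports 213 infants enrolled with recruitment continuing, so at that stage this could be fixed before the final analysis. The downside is lower power for non-uniform effects, as Step 6 shows. A departure from proportional odds affects the meaning of the common odds ratio and the power of the rank test, but not the rank test's type I error.
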